| 1. **Selection of comparison group(s) or controls**   In the cohort and cross-sectional studies outlined in objectives 1-4 we will compare rates of antibiotic prescribing and infection-related outcomes in different population sub-groups which will be defined by age-group, gender, SES, co-morbidity, smoking status and obesity.  To assess the number needed to treat with antibiotics to avoid one infection-related adverse event (objective 4) we will compare patients who have been treated with antibiotics (cases) to those who have not been treated with antibiotics (controls)  Objective 5 is limited to prediction and does not attempt comparison. |

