| 1. **Data/ Statistical Analysis**   *1. Estimate the incidence of i) GP consultations for infection and ii) antibiotic prescriptions*  For every patient in cohort 1, data on all consultations for infection and antibiotic prescriptions occurring within the study period will be extracted. We will estimate the incidence of GP consultations for infection and antibiotic prescriptions. This will be done for all consultations and prescriptions, and then separately for each category of infection and each class of antibiotics, based on chapter 5.1 of the British National Formulary (BNF) (see Appendix Tables 1 & 2). The denominator will be estimated as total person-time contributed by patients in the cohort during the study period. We will use Poisson regression to estimate the adjusted rate of consultation and prescription, taking account of the effect of age, gender, SES, ethnicity, selected co-morbidity, smoking and obesity. Random effects will be included to take account of clustering of observations by practice. Rates will be assessed for overdispersion by additionally fitting a negative binomial model and testing for alpha greater than zero via a likelihood-ratio test. If rates are found to be overdispersed, the negative binomial model will be used instead of a Poisson model. Adjusted rate ratios will be presented with 95%-confidence intervals.  *2. Describe antibiotic prescribing patterns linked to the reason for prescription*  The overall number of antibiotic prescribing episodes will be calculated for each patient individually, counting all recorded prescriptions between 1st April 2007 and 31st December 2015. For each episode, a clinical indication will be ascertained. Read codes for a diagnosis or symptom of infection recorded on the same day as the antibiotic prescription will be assumed to represent an indication for the prescription. Where more than one possible indication within the same type of infection is recorded on the day of prescription, the more granular code will be used. If multiple indications across different types of infection are recorded, the prescription will be labelled as having multiple indications. Conversely, if no infectious indication for a prescription was found, the prescription will be labelled as having no infectious indication and we will look for any non-infectious codes associated with the date of antibiotic prescription. The ten most common indications will be established and compared to the same numbers for the period from 1998-2001.14 This approach will be replicated for each class of antibiotics based on chapter 5.1 of the BNF. Patterns of repeat consultation or prescription during episodes of infection which may be prolonged will be investigated for each antibiotic prescription extracted in objective 1. We will define a new episode as a consultation or prescription recorded at least 28 days after any previous consultation for infection or antibiotic prescription. We will undertake sensitivity analyses to investigate the impact of using different time periods to define an episode. We will also examine the use of regular (prophylactic) antibiotic treatment.  Proportions and appropriate 95%-confidence intervals will be calculated and all results will be stratified by age-group, gender, SES, ethnicity, selected co-morbidity, obesity and smoking status. Descriptive data will be displayed graphically.  *3. Estimate the incidence of adverse outcomes in the following 28 days*  For each of the selected clinical infection syndromes in the nested cohort study, events in CPRD, HES and ONS will be searched for all adverse outcomes of interest (see *M.* Exposures, Health Outcomes§ and Covariates). Crude incidence rates of for each outcome will be calculated for patients who were treated (exposed) and not treated (unexposed) with an antibiotic. The denominator will be estimated as the total person-time contributed by patients at risk of each adverse outcome, taking account of the fact that this will be different for each outcome. For example, exposed and unexposed patients cannot consult General Practice if they have been admitted to hospital and should therefore not contribute to the denominator during this period when estimating rates of GP re-consultation in the 28 days following consultation for infection. A Poisson regression model will be used to estimate adjusted rates of adverse outcomes in each group, controlling for age, gender, socio-economic status, ethnicity, co-morbidity, obesity and smoking status and assessing for interaction between age and co-morbidity. Random effects will be included to take account of clustering of observations by practice. If the outcomes are overdispersed, negative binomial models will be used instead of Poisson models. Adjusted rate ratios will be presented with 95%-confidence intervals.  *4. Estimate the number of patients needed to treat with antibiotics to avoid one infection-related adverse outcome*  For each clinical infection syndrome-related adverse outcome identified in objective 3, the odds of that outcome in the 28 days following consultation for those treated with antibiotics (unexposed) and not treated with antibiotics (exposed) will be estimated using logistic regression. We will calculate adjusted odds ratios for the protective effect of antibiotics, adjusting for age, gender, SES, ethnicity, year/season, co-morbidity and the probability of receiving antibiotic treatment (see *O. Plan for addressing confounding*) and assessing for interactions with age and co-morbidity. We will use mixed models to adjust for clustering at a practice level and to take account of clustering of observations within a patient due to repeat episodes of infection. Where there is a significant effect of antibiotics between treated and untreated patients, the NNT or NNH to prevent one individual from developing an adverse outcome is calculated as *1/(absolute risk difference)*. A significant effect will be defined by a p-value < 0.05 for the coefficients of antibiotic treatment and its interactions. To avoid an arbitrary cut-off point, p-values close to 0.05 will also be assessed but discussed separately. The NNT will then be used to assess the clinical relevance of any significant differences found. Whilst the relative risk reduction (RRR) may be similar, the NNT may be different due to differing background risk. This will be explored.  *5. Develop risk prediction tools to support clinical decision making*  For each cohort (i.e. for each of the clinical syndromes of UTI, RTI and SSTI), we will develop a logistic regression risk model to predict the risk of adverse outcomes if patients are treated versus not treated with antibiotics. Models will be developed on a random sample of 80% of the observations within a cohort, reserving 20% of the data to estimate the model’s predictive performance.  A negative outcome will be defined as the occurrence of any of the following within 28 days following the index consultation: hospital admission for infection or complication; re-consultation for infection; A&E admission; death. Antibiotic treatment will be defined as a prescription of an antibiotic on the day of consultation for clinical syndrome. Risk factors will be selected based on the analyses outlined in objectives 1-4 and broadly grouped into: socio-demographic variables, co-morbidity and clinical presentation. Biologically plausible interactions between risk factors and age and between risk factors and co-morbidities will be examined.  Whereas age and sex will be forced into the model, other risk factors will be added in order of their significance in objective 4. Risk factors will be kept in the model if they improve the predictive performance of the model as defined by model discrimination and model calibration.17 For example, a risk factor will be used in the model if it improves discrimination and/or calibration. If a variable improves discrimination but reduces calibration, it will still be included in the model, but will be omitted if it increases calibration at the cost of discrimination.  Model discrimination, i.e. the model’s ability to correctly identify patients with and without an outcome, will be estimated using the concordance (c) statistic.18 The c statistic represents the probability that between two randomly chosen patients, one with the outcome and one without, the model assigns a higher score to the patient with the outcome. As a second measure, model calibration will be assessed using the Hosmer-Lemeshow test.18 We will additionally assess model calibration graphically for reasons for poor calibration by comparing the mean observed outcome in deciles of predicted risk. In this calibration plot, the intercept indicates the extent to which predictions are systematically too low or too high, while the slope reflects overfitting of the model.  For each model, we will estimate the internal validity of discrimination and calibration estimates using cross-validation with bootstrap subsampling based on 1000 iterations. In a secondary analysis, we will assess model performance in subgroups by age, sex and co-morbidity.  Finally, we will develop a simplified scoring system using the risk factors in the model,17 assigning the total score to a specific absolute risk of adverse outcomes in the 28 days following consultation, comparing outcomes if an individual is treated versus not treated with antibiotics. We will assess the predictive performance of the risk scores using the approaches outlined above. |

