| 1. **Plan for addressing confounding**   In objectives 1-3 the aim is to describe rates and undertake descriptive analyses rather than to make inferences about the effect of antibiotic treatment, which is the purpose of objectives 4 and 5. For this reason the issue of confounding is only relevant to objectives 4 and 5.  Individuals who are at higher risk of complications will be more likely to be prescribed antibiotics by their GP (i.e. confounding by indication), introducing a systematic difference between those who are treated and not treated with antibiotics. In this scenario, untreated cases will be less likely to experience adverse events irrespective of their exposure to antibiotics, tending to underestimate the protective effect of antibiotics. We will use propensity score methods to attempt to adjust for this issue. These methods are increasingly used to mitigate the consequences of non-random allocation of treatment in observational studies by modelling the a priori probability of each patient to receive the treatment.  We will use the treatment propensity scores to perform an inverse probability of treatment weighting to account for baseline differences in treated and untreated participants. This will enable assessment of absolute risk and numbers needed to treat to prevent re-consultation and hospitalisation in different groups.19 Propensity score weighting in effect produces a synthetic sample in which the distribution of measured baseline covariates is independent of treatment assignment. Presentation and analyses of results are very similar to a randomized trial allowing assessment of absolute risk and numbers needed to treat in different groups.  In order to create appropriate propensity scores, we will attempt to capture indicators for severity of disease and patients’ risk of complication, such as prior hospitalisation and immunosuppression. Measures such as vital signs are usually poorly recorded which can hamper efforts to estimate disease severity. To overcome this issue we will use GP prescribing preference as an instrumental variables, as described by Davies et al 2013.20  Besides confounding by indication, a number of further factors might influence prescribing. The decision to prescribe an antibiotic is a complex process, depending on multiple characteristics on the patient and practice level. Patients’ demographic factors, patients’ attitude towards antibiotic prescribing, physicians’ workload, date of consultation and geographic location of the practice have been found to influence physicians’ prescribing decisions.21 The use of further instrumental variables may help to estimate the impact of these factors in our analysis and we will also control for differences in prescribing habits between practices through the application of random effects models taking account of potential correlation within multiple episodes of the same patient and between patients within the same practice.  Acknowledging that differences in practice prescribing do not necessarily constitute actually differing prescribing habits but might instead reflect underlying differences in coding, we will undertake an exploratory analysis to look at variation between practices graphically. Using a novel approach we will visualise variability between multiple data-generating sources (i.e. practices) that was specifically designed and tested for multitype, multivariate and multimodal biomedical data.22,23 Where outlying practices are identified, analysis will be re-run without those practices and results presented with the analysis outlined in *N. Data/ Statistical Analysis*. |

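### The Objective 5 tool displays a treated-versus-untreated risk, but its model-building steps do not carry over the protocol's confounding plan, and another section denies that any comparison is made

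*Protocol*

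**What the plan says.** Under Data/Statistical Analysis, step 5, for each syndrome cohort "we will develop a logistic regression risk model to predict the risk of adverse outcomes if patients are treated versus not treated with antibiotics". The simplified score built from it is for "comparing outcomes if an individual is treated versus not treated with antibiotics".

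The candidate variables are "broadly grouped into: socio-demographic variables, co-morbidity and clinical presentation". The building rule is: "Whereas age and sex will be forced into the model, other risk factors will be added in order of their significance in objective 4". Then: "Risk factors will be kept in the model if they improve the predictive performance of the model as defined by model discrimination and model calibration". A variable that improves discrimination but worsens calibration stays; one in the opposite position "will be omitted if it increases calibration at the cost of discrimination". The interactions to be examined are those of risk factors with age and with co-morbidities.

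Step 4 of the same section adjusts for the probability of receiving an antibiotic and assesses interactions of the antibiotic effect with age and co-morbidity.

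The Plan for addressing confounding explains that Objectives 1 to 3 are descriptive, whereas inference about antibiotic treatment belongs to Objectives 4 and 5: "For this reason the issue of confounding is only relevant to objectives 4 and 5". It plans propensity scores, inverse probability of treatment weighting (IPTW) and GP prescribing preference as an instrument.

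The section on comparison groups says: "Objective 5 is limited to prediction and does not attempt comparison".

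**The concern.** A model that predicts risk under the care patients actually received can be built on predictive performance alone. A model that tells a GP what a patient's risk would be with and without an antibiotic cannot, because the difference between its two outputs is a treatment effect. The protocol describes the second kind of output and writes the building rule of the first kind.

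The protocol itself expects higher-risk patients to be treated more often, so that the protective effect is underestimated. If step 5 is carried out as written, the contrast shown to users may carry that bias and may differ from the contrast reported under Objective 4 for the same cohort. The tool is meant to support prescribing decisions, so this is the number on which its users would rely.

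**Working it through.** **1. The passages side by side**

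| Question | Step 4 | Step 5 | Confounding section | Comparison-group section |
|---|---|---|---|---|
| Is an antibiotic contrast estimated or shown? | Yes | Yes | Yes, Objectives 4 and 5 | Not for Objective 5 |
| Is confounding control named? | Probability of treatment | None | Propensity score, IPTW, instrument | Not addressed |
| Are antibiotic interactions named? | With age and co-morbidity | None | Not addressed | Not addressed |
| What is forced in? | Adjustment list | Age and sex | Not addressed | Not addressed |

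The contradiction needs no assumption. There is also a gap in the candidate list. The confounding section intends to use severity indicators such as prior hospitalisation for the propensity score, but these are not clearly within step 5's three groups.

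**2. Inputs for a sense of size**

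Sample size considerations gives an antibiotic odds ratio of 0.69, an outcome risk of 2.4%, 5% significance and 80% power. The treated share s is not in the text. It can be inferred from the stated sample sizes with

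N = (z₀.₉₇₅ + z₀.₈₀)² × [1/((1−s)p₀(1−p₀)) + 1/(s·p₁(1−p₁))] / (ln OR)²

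where p₀ = 0.024 is the untreated risk and p₁ = 0.01668 follows from the odds ratio. With s = 0.80:

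N = 7.849 × (213.46 + 76.19) / 0.13769 = 16,511 (stated: 16,512).

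The same formula returns 971,057 at a risk of 0.04%, as stated, and a detectable odds ratio of 0.9753 at 3,355,353 records (stated: 0.975). So 80% treated is an inference that fits. I also show 50%.

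Without confounding the contrast is 2.40% against 1.67%: a difference of 0.73 percentage points, NNT = 1/0.00732 ≈ 137.

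**3. What an unadjusted contrast could show**

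Assume a binary severity marker with 20% prevalence that is not in the model. It multiplies the odds of prescribing by A and the odds of the outcome by B. The intercepts are set to keep the treated share and the 2.4% untreated risk. The observed risk in arm t is

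r_t = Σ_k P(severity = k | t) × risk(k, t).

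| A, B | 80% treated: untreated / treated risk, OR | 50% treated: untreated / treated risk, OR |
|---|---|---|
| 2, 2 | 2.25% / 1.70%, 0.75 | 2.29% / 1.74%, 0.76 |
| 3, 3 | 2.03% / 1.74%, 0.85 | 2.12% / 1.87%, 0.88 |
| 3, 5 | 1.83% / 1.78%, 0.97 | 1.97% / 1.98%, 1.00 |
| 5, 5 | 1.67% / 1.81%, 1.08 | 1.81% / 2.10%, 1.16 |

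One cell in full (80% treated, A = B = 5): 5.8% of untreated and 23.5% of treated patients are severe. The risks for non-severe and severe patients are 1.37% and 6.51% untreated, and 0.95% and 4.58% treated. Untreated: 0.942 × 1.37 + 0.058 × 6.51 = 1.67%. Treated: 0.765 × 0.95 + 0.235 × 4.58 = 1.81% (unrounded inputs). The true risks are 2.40% and 1.68%.

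**4. What the remedy can and cannot do**

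A simulation used one measured and one unmeasured severity variable of equal strength, 80% treated and a true odds ratio of 0.69. Effects on prescribing and outcome were 0.5/0.5, 0.5/0.8 and 0.8/0.8 log-odds per SD. Plain regression on the measured variable gave about 0.89, 1.03 and 1.29. Adding IPTW on that variable gave 0.90, 1.03 and 1.30. Rerunning moved these by up to about 0.05, but the two methods stayed within about 0.01 of each other. With both variables in the model, plain regression returned 0.69 to 0.71. The measured variable raised the c statistic by about 0.12 to 0.17.

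Omitting a measured confounder such as prior hospitalisation moved the odds ratio by about 0.03 to 0.05 in separate runs.

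**5. The retention rule, if it were applied to treatment**

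With 50% treated and an assumed SD of 0.5 to 1.2 for the rest of the linear predictor, the antibiotic term adds 0.003 to 0.009 to the c statistic at OR 0.69, 0.0002 to 0.0007 at 0.90, and about zero at 0.99.

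**The case against.** The strongest reply is that the confounding section expressly covers Objective 5, the limitations section names the same methods as the answer to severity confounding, and Objective 5 is described as a synthesis of Objectives 1 to 4. Step 5's silence need not mean exclusion. This stands against any claim that the protocol has no confounding control for Objective 5. It does not settle how that control enters the model.

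Second, a reader might infer that the rule can drop the antibiotic term, leaving identical treated and untreated risks. The documents do not support that as a stated plan. Treatment is defined separately from the risk factors, belongs to none of their groups, and is needed for the stated output. The increments in item 5 show only that its retention should not be left to the rule. Retention is unstated; it is not denied.

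Third, a reader might infer that the tool would show no benefit or harm. That rests on strong severity confounding which is assumed and unmeasured. Where it exists, weighting on recorded variables leaves it in place (item 4). A strong measured confounder would usually survive the selection rule because it predicts the outcome.

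Finally, how weights enter a prediction model is often left to an analysis plan. That would excuse silence. Here, however, the protocol fixes a selection algorithm unsuited to the output, and two of its sections disagree on whether a comparison exists.

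**Conclusion.** The point holds in a limited form. The protocol contradicts itself on whether Objective 5 makes a comparison. Its step 5 procedure is predictive while its output is a treatment contrast. The confounding plan is declared relevant to Objective 5 but is not carried into the model, and no antibiotic interactions are named there, although the study hypothesis is that protection differs between patient groups.

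The likely consequence is an understated benefit and a contrast that may not match Objective 4. In the illustration, a moderate unmeasured marker (odds ratios of 2 to 3) moves 0.69 to between 0.75 and 0.88, and the risk reduction falls from 0.73 to between about 0.55 and 0.26 percentage points. The effect vanishes or reverses only when the marker's odds ratio for the outcome is about 5 and that for prescribing is 3 to 5.

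These figures rest on the assumed severity marker, on a treated share inferred as 80% (50% also shown), and on 2.4% as the untreated risk. They illustrate possible bias and do not predict the study's result. The contradiction and the unsuited selection rule rest on the text alone.

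**What to change.** 1. In the comparison-group section, delete or correct the sentence on Objective 5 so that it agrees with step 5 and the confounding section.
2. In step 5, force in antibiotic treatment, its prespecified interactions with age and each co-morbidity of interest, and every variable in the propensity score. Covariates added by amendment for bias control can enter as confounders only, in line with the amendment's decision not to interpret their effects on the NNT. Apply the discrimination and calibration rule only to the remaining prognostic variables.
3. State that the displayed contrast comes from the confounding-adjusted Objective 4 analysis: IPTW, with the instrumental-variable estimate reported beside it as a check for unmeasured severity. Say what will be done if the two disagree materially. This helps only as far as the Objective 4 analysis itself removes severity confounding.
4. If the contrast cannot be supported in this way, withdraw the treated-versus-untreated output.

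The cost is amendment wording, one extra fit per syndrome, a few more variables in the score and possibly a marginally lower c statistic. No new data are needed.

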| 1. **Technical Summary (Max. 200 words**)**§**   **§***Please note:**This information will be published on CPRD’s website as part of its transparency policy*  Antibiotic overuse drives antimicrobial resistance. In primary care rates of antibiotic prescribing vary widely, associated with characteristics of the patient and GP prescribing behaviour.  The aim of this study is to investigate whether analyses of patient level characteristics can guide antibiotic prescribing decisions in primary care.  Using data from patients who contributed to CPRD between April 2007 and December 2015, we will describe the diagnosis, antibiotic treatment and clinical outcomes of patients with common infection syndromes. These analyses will be stratified by patient characteristics including: age, gender, social deprivation, selected co-morbidities, obesity and smoking.  In a series of cohort studies of patients with common infection syndromes, we will: a) estimate the rate of adverse outcomes comparing those who were treated with antibiotics to those who were not, using Poisson regression and b) calculate the number needed to treat to avoid one infection related adverse outcome using multi-level logistic regression, taking account of patient’s vulnerability through the use of propensity scores. These analyses will be stratified by each of the patient characteristics listed above. This work will be synthesized through models that predict each patient’s risk of adverse outcomes, comparing the scenario of antibiotic treatment versus no antibiotic treatment. |

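### The step 5 keep/drop rule lets any fall in the c statistic overrule better calibration, so the tool can show small high-risk groups a biased absolute risk

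*Protocol*

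**What the plan says.** The rule is in the Protocol, section N (Data/ Statistical Analysis), step 5. The default comes first: "a risk factor will be used in the model if it improves discrimination and/or calibration". The next sentence deals with conflicts. Of a variable that raises discrimination but harms calibration it says: "it will still be included in the model, but will be omitted if it increases calibration at the cost of discrimination".

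Protection from the rule is narrow: "Whereas age and sex will be forced into the model", and nothing else is forced. Co-morbidity terms and interactions are candidates only.

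Discrimination "will be estimated using the concordance (c) statistic", which the Protocol itself describes as a probability that a patient with the outcome is ranked above one without. On the other criterion: "As a second measure, model calibration will be assessed using the Hosmer-Lemeshow test", supplemented by a plot over deciles of predicted risk.

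The end product is a score tied to an absolute risk for each patient if treated and if not. The Technical Summary describes the same purpose: "comparing the scenario of antibiotic treatment versus no antibiotic treatment". Performance by age, sex and co-morbidity is a secondary analysis. No route is given from that analysis back to a dropped term, and no recalibration step is described.

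**The concern.** A tool that displays an absolute risk needs that number to be right in the group to which the patient belongs. That is calibration. The c statistic sees only the order of patients. A term that matters to a small group hardly changes the overall order, so its effect on c is tiny and chance can decide its sign. It may still change that group's risk substantially.

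The Protocol's objectives centre on differences by age and co-morbidity, so the terms most exposed to the rule are those the study most wants to get right. If such a term is lost, overall performance looks unchanged while the risks shown to the affected group are off.

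**Working it through.** The rule contains no figure to reproduce, so the check is of its logic and of what it can do.

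**1. What the rule amounts to.**

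| Change in c | Calibration better | Calibration worse |
|---|---|---|
| c rises | keep | keep |
| c falls | omit | omit |

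The sign of the change in c decides all four cells. Calibration decides only when c does not move at all.

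**2. How far c and absolute risk move for a real term.** Inputs from section I: outcome risk 2.4%, antibiotic OR 0.69, and interaction OR 0.83 (given there as a detectable effect, used here as an illustration). Assumed: age mix, prescribing pattern, co-morbidity main effect and 3% co-morbidity prevalence. In an exact population fit, adding the true antibiotic-by-co-morbidity term raises c from 0.57175 to 0.57187, a gain of 0.00012. The co-morbid group's untreated/treated risks move from 4.30%/3.06% to the true 4.70%/2.81%. The displayed benefit goes from 1.24 to 1.89 percentage points.

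**3. The same contrast by hand.** With o = p0/(1 − p0) and p1 = OR·o/(1 + OR·o), p0 = 2.4% gives o = 0.02459.
- Without the term: OR 0.69, p1 = 1.67%, difference 0.73 points.
- With it: OR 0.69 × 0.83 = 0.573, p1 = 1.39%, difference 1.01 points.

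**4. How often chance makes c fall although the term is real.** Sets A to D test a co-morbidity-by-age-85+ term. The co-morbidity log-odds is 0.7 below 85 and 0.3, 0.0 or 1.1 from 85 up; the cell holds about 0.65–0.67% of episodes; overall risk is 2.4%. The sets differ in assumed population. Set E is the interaction in step 2. Sets A, B, C and E used 300 runs per setting. Entries are the percentage of runs in which c fell **on the development data**; three values are the three log-odds in that order.

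| Set | 671,070 episodes | 3,355,353 episodes |
|---|---|---|
| A | 25, 2, 30 | 4, 0, 15 |
| B | 22, 2, 37 | 6, 0, 28 |
| C | 10, 0, 17 | 2, 0, 1 |
| D (0.3 only) | 7 | 1 |
| E | 19 | 3 |

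The range is 0–37%. In set A the term was significant by likelihood-ratio test in every run.

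If terms were instead judged on the 20% hold-out, the rates are mostly higher. Set D gives 32% and 16%; set E gives 45% and 30%.

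**5. How much of this is the veto.** A term that improves neither measure fails the default rule anyway. In set D, c fell and Hosmer-Lemeshow improved in 6% (of 7%) and 1% (of 1%) of development runs, and in 20% (of 32%) and 9% (of 16%) of hold-out runs. In set C on the hold-out at 671,070, the veto accounted for about 13 of 30, 8 of 13 and 19 of 32 percentage points.

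**6. What the group is shown when the term is lost (set A).** The last two columns apply OR 0.69 to each risk, taken as the untreated risk, with the formula in step 3.

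| Log-odds from 85 | Shown | True | Implied difference shown | True difference |
|---|---|---|---|---|
| 0.3 | 7.5% | 5.9% | 2.20 points | 1.75 points |
| 0.0 | 7.2% | 4.4% | 2.12 points | 1.32 points |
| 1.1 | 9.9% | 12.2% | 2.85 points | 3.45 points |

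With the term kept, true/predicted risk in the cell was 0.99–1.01. Set D, with its own assumed population, showed about 10.2% against 7.9% true.

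**7. When the rest of the model is misspecified.** Here c can fall in the population, not only by chance. In 4,000 random scenarios with an unmodelled age-by-co-morbidity effect, consider the terms that improved both overall fit and the worst group risk error. Among these, c fell for 881/3,961 (22%) antibiotic-by-co-morbidity terms and 351/3,740 (9%) co-morbidity terms.

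**The case against.** Several objections carry weight.

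- **The loss is conditional.** A reader might infer that calibrating terms are thrown out as a matter of course. The text does not say so. Only terms that lower c are lost, a true term in an otherwise correct model does not lower population c, and age and sex are safe.
- **The hold-out rates are not the natural reading.** The Protocol develops models on the 80% and reserves the 20% to estimate performance. It does not say terms are chosen on the 20%, so the development-data rates are the relevant ones.
- **Not every fall in c is the veto's doing.** Step 5 of the working shows this, most clearly on the hold-out.
- **The NNT is estimated elsewhere.** A reader might infer that the study's NNT is wrong. Step 4 estimates it from separate models that this rule does not touch, and section L confines objective 5 to prediction. Only the risk difference implied by the tool is exposed.
- **The two sentences need not contradict each other.** It is tempting to say that the and/or sentence and the omission clause clash. A default followed by a tie-breaker is a fair reading.
- **Gross miscalibration is unlikely.** Logistic regression with an intercept, fitted by maximum likelihood, matches observed to expected events overall in the development data. The error arises within groups.
- **Subgroup performance will be examined.** That could reveal a miscalibrated group.

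These narrow the point but do not remove it. The subgroup check has no stated power to restore a term, and Hosmer-Lemeshow over deciles pools a small group with everyone else at similar predicted risk.

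**Conclusion.** The point holds in conditional form. The tie-breaker gives the c statistic the decision whenever it moves, with no minimum difference, in a tool whose output is an absolute risk. It **can** therefore drop real co-morbidity or interaction terms and leave displayed risks biased in small high-risk groups. In the set A illustrations the group's true risk was about 0.62 to 1.24 times the displayed one.

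The 0–37% range shows that the mechanism operates at the Protocol's cohort sizes. It does not forecast this study. It rests on an assumed age mix, co-morbidity prevalence and effects, none of them in the Protocol, and on the 2.4% risk, which section I borrows from pneumonia. At an assumed 10% risk, set E's development-data rates drop to 3% at 671,070 and 0% at 3,355,353. The rule should be changed because it is unsuited to the tool's purpose and easily replaced.

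**What to change.** Replace the two keep/drop sentences in step 5 with the following:

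- Candidate terms are selected within the 80% development data on the model likelihood (AIC or penalised likelihood) or another proper score such as the Brier score, which rewards calibration and discrimination together.
- A term that improves calibration is not dropped because of a trivial fall in c. Calibration here means the slope and the observed/expected ratio, overall and by age and co-morbidity group.
- The c statistic is reported as a description of performance.

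The cost is two sentences and a little extra analysis, with no new data. The reported c statistic may be very slightly lower.
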